**Abstract**

**Context**

Botulinum toxin injections are a common treatment for managing spasticity resulting from central nervous system damage, including stroke, multiple sclerosis, and traumatic brain injury. However, the injections are associated with perceived pain, and many patients experience significant anticipatory stress regarding future sessions. The intensity of this stress varies among individuals.

Music therapy, particularly receptive musical interventions structured around a U-shaped sequence, promotes progressive relaxation through distinct musical phases. This method has demonstrated efficacy in reducing pain and anxiety across various clinical contexts, including chronic and acute pain, Alzheimer’s disease, fibromyalgia, and neurologically mediated pain. Given the painful nature of botulinum toxin injections, this study proposes the use of receptive music therapy to improve patient tolerance of the procedure. We hypothesize that receptive musical intervention can reduce injection-induced stress in adults undergoing botulinum toxin treatment. To our knowledge, no studies have specifically investigated the effect of music therapy on stress related to botulinum toxin injections.

**Objectives**

We aim to conduct a prospective randomized (1:1) controlled trial to evaluate the impact of receptive music intervention on stress levels, measured *via* heart rate variability (HRV), during botulinum toxin injection sessions.

**Secondary objectives** :

To evaluate the effect of exposure to a musical intervention session during botulinum toxin injections at Injection Visit 1 on:

- - Injection-induced stress as assessed by heart rate variability (HRV) parameters excluding the LF/HF ratio
  - Injection-induced pain
  - Anxiety related to injections
  - Patient satisfaction
  - The impact of the musical intervention on the medical procedure (botulinum toxin injections) as assessed by the physician at the end of the session

To evaluate the effect of exposure to a musical intervention session during Injection Visit 2, in order to assess the impact of repeated exposure to the musical intervention on:

- Injection-induced stress as assessed by HRV parameters excluding the LF/HF ratio
- Injection-induced pain
- Anxiety related to injections
- Patient satisfaction
- The impact of the musical intervention on the medical procedure (botulinum toxin injections) as assessed by the physician at the end of the session

**Study type:** Controlled, randomized, two-arm parallel design, waiting-list type study.

**Number of centers:** 1

**Study description:** This study will be conducted in patients regularly receiving botulinum toxin injections for spasticity management. The first injection session will be performed either with (IM-IM) or without (CT-IM) a musical intervention according to the randomization group; the subsequent injection session will be performed with a musical intervention. Patients will be allowed to choose their preferred music genre (Jazz, Classical, Electronic, R&B, Ambient, Rock, etc.) to benefit from a minimum 20-minute personalized musical intervention session (duration may vary depending on the number of injections performed).

**Primary outcome measure:** Heart rate variability.

**Number of subjects:** 80 participants

**Inclusion criteria:**

- Adult patients (male or female) with neurologically-originating spasticity (e.g., multiple sclerosis, stroke, traumatic brain injury) eligible for botulinum toxin injection treatments
- Patients known to experience pain and/or anxiety
- Ability to provide informed consent to participate in the research
- Affiliation with a social security system

**Exclusion criteria:**

- Contraindication to musical intervention (e.g., severe hearing impairment, unstable psychotic disorders, history of auditory trauma)
- Major cognitive impairment
- Any medical condition deemed by the investigator as incompatible with study participation
- Indication for sedation with nitrous oxyde during botulinum toxin injection sessions
- Medication or medical conditions potentially affecting heart rate variability during the study, including beta-blockers, antiarrhythmics, anxiolytics, benzodiazepines, antihypertensives, and calcium channel blockers
- Pregnant or breastfeeding women
- Refusal to participate

**Brief description of the intervention:** The MUSIC CARE® device will be used, a personalized yet standardized musical intervention following a specific rhythm pattern ("U-sequence"), delivered via a tablet application.

**Study procedures:** Patients will be recruited from the cohort of individuals regularly treated with botulinum toxin injections in the Physical Medicine and Rehabilitation (PMR) department at Clermont-Ferrand University Hospital. Botulinum toxin injections will be administered in the PMR department. Each patient’s participation duration will be up to 4 months.

## Ethics Committee

CPP Sud-Méditerranée IV

## Study Timeline

Ethics Committee Submission: January 2025

Study Start: April 2025

Recruitment Period: 2 years

Follow-up Period: 4 months

Total Study Duration: 32 months

Estimated Study End (last visit of last patient): October 2027

Final Study Report: October 2028

# STUDY RATIONALE / SCIENTIFIC JUSTIFICATION

## Current state of scientific knowledge

The efficacy of botulinum toxin (BT) injections for spasticity has been widely demonstrated following stroke (1). Consequently, this treatment is used in numerous patients with central neurological deficits (stroke, multiple sclerosis, spinal cord injury, traumatic brain injury). The effect of botulinum toxin is temporary (approximately 3 months), thus intramuscular injections must be repeated every 3 to 4 months.

Regarding botulinum toxin, it has been shown that intramuscular injections reduce hypertonia (1). Indeed, BT has been the reference treatment for focal spasticity since the 2011 ANSM guidelines (2). Tolerance to injections varies among patients. Pain experienced during the injection is primarily related to skin puncture (3) but may also be linked to the localization technique used (electrical stimulation) or the injection site (palmar and plantar injections being the most painful). This pain induces significant stress in most patients during injection.

Since prehistoric times, music has been integrated into the treatment of various conditions (4). Since the 1960s, music has been reintroduced for therapeutic purposes, and musical interventions have been used to alleviate pain and distress in patients with various medical conditions, particularly for chronic and acute pain management (5,6). A recent meta-analysis revealed that musical interventions positively affect pain intensity, emotional distress, use of anesthetics and opioid and non-opioid agents, heart rate, systolic and diastolic blood pressure, as well as respiratory rate (7). However, contradictory results have been observed, likely due to the wide variability of musical interventions across studies, differing in duration, frequency, style, genre, preparation, selection, and implementation methods (7). To address these inconsistencies, recommendations have been formulated regarding musical interventions in clinical practice (8,9).

In line with these recommendations, a standardized musical intervention based on a web application was developed at the University Hospital of Montpellier. This is the “U-shaped” composition sequence. This musical sequence ranges from 20 to 60 minutes and is divided into several stages that progressively allow the patient to relax according to the “U” technique (8–11). This application now enables controlled use of musical interventions in medical settings via a tablet. Based on the “U” sequence, the MUSIC CARE® program is an application allowing patients to listen to a variety of pre-recorded music pieces performed by professionals.

Several studies have focused on stress management, pain reduction, anxiety relief, and quality of life improvement in patients with various pathologies and painful conditions (cataract surgery (12,13), migraine treatment(14), coronary angiography(15), cancer treatment (16)).

Few studies have investigated pain experienced during injections. The only published studies concern the effect of localization technique.

To our knowledge, no clinical trials have specifically examined the use of musical intervention associated with BT injections in the treatment of spasticity. Furthermore, botulinum toxin injections used in Physical Medicine and Rehabilitation (PMR) for spasticity treatment in patients with stroke, multiple sclerosis (MS), or traumatic brain injury are potentially painful and stressful due to needle penetration through the skin barrier.

The objective of this study is to evaluate the effect of exposure to a musical intervention session during botulinum toxin injections on injection-induced stress.

## Current state of preclinical research

Not applicable.

## Hypotheses and objectives

The hypothesis of this research is that a musical intervention can reduce stress in adults during botulinum toxin injections.

The primary objective of the study is to assess the effect of exposure to a musical intervention session during botulinum toxin injections on injection-induced stress, measured by Heart Rate Variability (HRV).

Secondary objectives include evaluating the effect of exposure to a musical intervention session during botulinum toxin injections on injection-induced pain and anxiety. Additionally, patient satisfaction regarding the injections following the musical intervention session will be assessed. The impact of the musical intervention on the medical procedure will be evaluated based on the physician’s appraisal at the end of the session. Finally, the patient’s perception of time during the session will also be evaluated.

## Summary of expected benefits and known or foreseeable risks for participants

The expected benefit for patients is a reduction in pain and stress during injections through the use of a musical intervention. Additionally, patient isolation with music is anticipated to promote greater relaxation regarding the upcoming medical procedure. The patient’s perception of time may also be altered by the use of the musical intervention. There are no known risks associated with the use of the MUSIC CARE® device.

## Expected outcomes

## The objective is to improve the tolerance of botulinum toxin injections in patients through the use of a musical intervention. We therefore aim to reduce stress and anxiety associated with the medical procedure. Additionally, we hope to create a therapeutic sound environment that promotes relaxation, alleviates pain, and enhances the emotional and physical well-being of patients prior to botulinum toxin injections.

# STUDY OBJECTIVES

## Primary objective

We aim to conduct a prospective randomized (1:1) controlled trial to evaluate the impact of receptive music intervention on stress levels, measured via Heart Rate Variability (HRV), during botulinum toxin injection sessions.

## Secondary objectives

To evaluate the effect of exposure to a musical intervention session during botulinum toxin injections at Injection Visit 1 on:

- - Injection-induced stress as assessed by HRV parameters excluding the LF/HF ratio
  - Injection-induced pain
  - Anxiety related to injections
  - Patient satisfaction
  - The impact of the musical intervention on the medical procedure (botulinum toxin injections) as assessed by the physician at the end of the session

To evaluate the effect of exposure to a musical intervention session during Injection Visit 2, in order to assess the impact of repeated exposure to the musical intervention on:

- Injection-induced stress as assessed by HRV parameters excluding the LF/HF ratio
- Injection-induced pain
- Anxiety related to injections
- Patient satisfaction
- The impact of the musical intervention on the medical procedure (botulinum toxin injections) as assessed by the physician at the end of the session

# STUDY DESCRIPTION

## Type of trial

Controlled, randomized, two-arm parallel design, waiting-list type study.

## Research category

This study is classified as a Category 2 interventional research involving human participants (with minimal risks and constraints), and does not involve a health product.

## Justification of qualification

**Intervention Type 1**, according to the French Decree of April 12, 2018, establishing the list of research activities referred to in Article L.1121-1, 2° of the French Public Health Code: *Random allocation of one or more diagnostic or medical procedures or routine practice interventions to an individual or a group of individuals.*

The MUSIC CARE application does not meet the definition of a medical device (MD) as outlined in Article 2.1 of Regulation (EU) 2017/745 on medical devices.

# STUDY POPULATION

## Inclusion Criteria

- Adult patients (male or female) with neurologically-originating spasticity (e.g., multiple sclerosis, stroke, traumatic brain injury) eligible for botulinum toxin injection treatments
- Patients known to experience pain and/or anxiety
- Ability to provide informed consent to participate in the research
- Affiliation with a social security system

## Exclusion Criteria

- Contraindication to musical intervention (e.g., severe hearing impairment, unstable psychotic disorders, history of auditory trauma)
- Major cognitive impairment
- Any medical condition deemed by the investigator as incompatible with study participation
- Indication for sedation with nitrous oxyde during botulinum toxin injection sessions
- Medication or medical conditions potentially affecting heart rate variability during the study, including beta-blockers, antiarrhythmics, anxiolytics, benzodiazepines, antihypertensives, and calcium channel blockers
- Pregnant or breastfeeding women
- Refusal to participate

## Procedures for premature study discontinuation

The investigator may intervene at any time and discontinue the protocol if, in their judgment, the patient’s health status no longer allows continued participation.

For any premature withdrawal from the study, the date and reason will be recorded in the subject’s case report form (CRF).

A participant may be withdrawn prematurely from the study for the following reasons:

- Intercurrent illness interfering with the normal course of the protocol
- Death
- Subject’s decision
- Major protocol deviation
- Lost to follow-up (a subject is considered lost to follow-up if they fail to attend a scheduled visit and cannot be contacted despite all reasonable efforts. The reason “lost to follow-up” will only be used if the investigation remains unsuccessful).

The study may be temporarily or permanently discontinued for the following reasons:

- Insufficient or no recruitment
- Inability to secure study funding
- Any directive from regulatory authorities requiring temporary or permanent discontinuation
- Decision by the sponsor and coordinating investigator

Any temporary or permanent discontinuation, as well as the end of the study, will be notified to the Ethics Committee (CPP) and the French Medicines Agency (ANSM) within the legal timeframes.

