# STUDY METHODOLOGY

## Evaluation criteria

### Primary endpoint

Patient stress, assessed during Injection Visit #1, will be estimated by changes in Heart Rate Variability (HRV), measured before and during the botulinum toxin injection session using the LF/HF ratio.

The LF/HF ratio is a reliable indicator of the balance between sympathetic and parasympathetic nervous system activity. It provides insight into stress regulation, cardiovascular health, and physiological adaptation. A lower LF/HF ratio may be associated with improved recovery, better emotional regulation, and a healthier autonomic nervous system balance.

HRV will be measured using a Polar H10 heart rate monitor belt. Data will be exported to the Elite HRV application and analyzed using KUBIOS software.

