**V1 (Month 0): Injection visit 1 (inclusion visit)**
At this visit, informed consent will be obtained from the patient or their legal guardian. The physician will provide a copy of the signed consent form to the patient or their legal representative/trustee/designated person. The following data will be collected: age, sex, pathology, and date of first botulinum toxin injection. Once this information is recorded, randomization will be performed by the Clinical Research Associate (CRA) of the department.
For all injections, the same standardized protocol will be applied for each patient (ultrasound-guided or electromyography localization technique, MYOBOT needle [26G], analgesia by ice for palmar or plantar injections upon patient request) in an outpatient setting.

During the first injection visit, a Polar H10 heart rate monitor chest strap will be placed on the patient to measure stress induced by the medical procedure. A minimum recording period of 10 minutes is required prior to the injections to collect reliable baseline data. During this time, the physician will prepare the syringes for botulinum toxin injection. The patient will complete the self-administered anxiety questionnaire (STAI-Y1).

The control group (CT-IM) will not receive any specific intervention other than the Polar H10 heart rate monitor. This group will undergo botulinum toxin injections according to usual practice within the department, with the same evaluations as the intervention group (IM-IM).

The intervention group (IM-IM) will receive a tablet and headphones to listen to music during the botulinum toxin injections. Before the injection, during the waiting time, the patient, with or without assistance, will choose the music to listen to based on personal preferences. The music duration can be adjusted to fit the length of the medical procedure.

At the end of the injection session (both groups), a Visual Analog Scale (VAS) will be presented to the patient to rate pain on a scale from 0 to 10. The nurse or CRA will ask the patient to rate their satisfaction with the intervention using a VAS. Anxiety will be measured using the STAI-Y1 questionnaire. Time perception will also be evaluated based on patient self-report and compared to the actual duration of the medical procedure.

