## Product presentation

A pair of headphones and a tablet will be available for the entire duration of the study. The headphones will be placed on the patient’s ears once they are positioned on the examination table. The nurse assisting the physician during the botulinum toxin injections will help the patient select the music they wish to listen to. Additionally, the patient may navigate through the application to modify the music style or adjust the duration of the listening session, if desired. The objective is to ensure that the listening duration extends throughout the medical procedure, continuing until the completion of the injections. The listening session may also be controlled by the investigator or the nurse, who can stop the device at any time.

[figure not shown]

**Figure 3** : Application MUSIC CARE^®^

The MUSIC CARE® application is available for download on various platforms (AppleStore or PlayStore). The PMR department will have an account to allow patients to benefit from this therapeutic approach. The first image in Figure 2 shows the different session choices based on the patient’s preferences. In the context of the MUSIBOT study, the application will be used with the aim of reducing stress related to the medical procedure. A diagram is then presented to explain to the patient the "U-shaped" sequence. Once the patient selects the "pain" program, another page appears, allowing the patient to choose the music style they wish to listen to during the session. Music can be selected by category. The patient selects the music to listen to and is then asked to rate their current level of pain using a Visual Analog Scale (VAS). The music begins according to the "U-shaped" sequence, with a minimum duration of 20 minutes. The duration can be adjusted based on the length of the medical procedure. The patient/nurse controls the application and can modify settings as needed.

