## Data analysis: general aspects

The statistical analyses will be conducted using Stata software (version 15, StataCorp, Texas, USA).

Continuous variables will be presented as mean and standard deviation or median and interquartile range, depending on their statistical distribution. The normality of continuous variables will be assessed using the Shapiro-Wilk test and the density curve. Categorical variables will be expressed as counts and percentages. Graphical representations will be provided whenever possible alongside the analyses.

The randomized groups will be compared at injection visit #1 according to the following variables: adherence to inclusion criteria, epidemiological characteristics, clinical characteristics, and treatments.

The initial comparability of the randomized groups will be evaluated based on key participant characteristics and potential factors associated with the primary outcome measure. Any differences between the groups on these characteristics will be determined based on clinical considerations, not solely statistical ones.

A description of protocol deviations, patients allocated based on these deviations, and reasons for withdrawal will also be provided. The number of enrolled patients and the enrollment curve will be presented by group.

The statistical analyses will first be performed according to the intention-to-treat (ITT) principle, including all patients except those who withdrew consent for the use of their data. A per-protocol analysis will be conducted by excluding patients who were not managed according to their assigned randomization group or who had major protocol deviations.

Comparisons between randomized groups will be conducted systematically (1) without adjustment and (2) with adjustment for factors that may have been imbalanced between the groups despite randomization.

The risk of a type I error will be set at a two-sided 5%. The analyses for secondary objectives will be exploratory in nature, and therefore, no correction for type I error will be applied.

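### Section 5.3 lets staff withdraw a patient from the study for a major protocol deviation, without saying that assessments continue, while the intention-to-treat analysis in section 10.2 counts on that patient's data

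*Protocol*

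**What the plan says.** Section 5.3 (Procedures for premature study discontinuation) introduces a list with "A participant may be withdrawn prematurely from the study for the following reasons", and one entry is "Major protocol deviation". The withdrawal is from the study, not only from the music. The section asks for the date and reason to be recorded. It does not say whether the remaining assessments are still made.

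Section 10.2 (Data analysis: general aspects) runs the ITT analysis first, "including all patients except those who withdrew consent for the use of their data". The per-protocol analysis is then formed by "excluding patients who were not managed according to their assigned randomization group or who had major protocol deviations".

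The timing matters. At injection visit 1 (section 7.1) consent and baseline data come first, and then: "Once this information is recorded, randomization will be performed by the Clinical Research Associate (CRA) of the department". The primary endpoint in section 6.1.1 is the change in LF/HF ratio from before to during the injections at that same visit. Pain, satisfaction, STAI-Y1, time perception and the physician's rating follow the injections. Visit 2 comes at month 3, give or take one month, and section 10.4 analyses it with mixed models.

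**The concern.** The two sections treat the same patients differently. For section 10.2, a major deviation decides which analysis set a patient belongs to. For section 5.3, it can end the patient's observation. An ITT analysis can include a deviator only if the outcome was measured, and no later choice in a statistical analysis plan can recover a measurement that was not made.

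The decision to withdraw would be taken after randomization, by staff who see whether the patient has a tablet and headphones. Missing data produced that way may be related to how the session went. To the extent that the permission is used, the patients with later outcomes in the ITT analysis come to resemble the per-protocol set, and the two analyses no longer check each other. This bears most on the repeated-exposure objective, which rests on visit 2.

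**Working it through.** **1. The two rules side by side, for a patient with a major deviation**

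- Section 5.3: may be withdrawn from the study; date and reason recorded; further assessments not mentioned.
- Section 10.2, ITT: included, unless consent for use of the data is withdrawn.
- Section 10.2, per-protocol: excluded.

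The ITT rule presupposes outcomes that section 5.3 allows staff not to collect. Nothing in the protocol says that data already collected are deleted.

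**2. What is lost, by time of withdrawal**

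- Between randomization and the end of the visit 1 recording, with the recording stopped: the primary LF/HF change, the post-session ratings and visit 2.
- After the recording but before the ratings: the ratings and visit 2. The primary value is kept.
- After visit 1 is complete: visit 2 only.

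Only the first case touches the primary endpoint.

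**3. Power**

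Inputs from section 10.1: difference 1.8, SD 2.3, two-sided 5%, power 90%.

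n per group = 2 × (1.960 + 1.282)² × (2.3/1.8)² = 2 × 10.51 × 1.633 = 34.3, so 35. This reproduces the plan's figure. The t-based calculation gives 35.3, so 36. The allowance is 40 − 35 = 5 per group, or 5/40 = 12.5%.

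Power if primary values are lost in both arms (the loss rates are assumptions):

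| Analysable per group | Loss | Power, normal | Power, t |
|---|---|---|---|
| 40 | 0% | 93.8% | 93.3% |
| 38 | 5% | 92.7% | 92.0% |
| 36 | 10% | 91.3% | 90.6% |
| 35 | 12.5% | 90.6% | 89.75% |

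Across this range the loss does not threaten power. What is left is selective missingness.

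**4. Size of a selective loss (illustration only)**

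Suppose a fraction f of one arm is lost, and those patients differ by s on average from the patients kept in that arm. The full-arm mean is (1 − f) × m + f × (m + s) = m + f × s, where m is the mean of those kept. The observed arm mean is therefore off by f × s.

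For the primary endpoint, and only if the LF/HF recording itself is lost:

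- f = 5%, s = 1.0: 0.05 × 1.0 = 0.05 points; 0.05/1.8 = 3%.
- f = 4/40 = 10%, s = 2.3 (1 SD): 0.10 × 2.3 = 0.23 points; 0.23/1.8 = 13%.
- f = 12.5%, s = 2.3: 0.125 × 2.3 = 0.29 points; 0.2875/1.8 = 16%.

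The protocol gives no SD for the secondary endpoints, so the same formula can only be put in SD units: 10% lost with a 1 SD difference shifts the arm mean by 0.10 SD. If both arms lose equal fractions with the same s, the shift cancels in the comparison. Both f and s are assumed; the protocol gives neither, nor the sign of s.

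**The case against.** The strongest reply is that section 5.3 is a generic, permissive list, placed beside death and loss to follow-up, and that section 10.2 would not keep deviators in the ITT set unless their data were meant to be retained. Section 6.3 also notes that loss to follow-up weighs less in this design because the primary objective is settled at visit 1. Section 10.5 allows multiple imputation, the mixed models use patients who have visit 1 data only, and section 10.2 promises to report deviations and reasons for withdrawal.

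Most of this stands, and it limits the point. It does not remove the conflict. A permissive rule still permits, and the protocol nowhere says that assessments continue. Imputation is optional. A mixed model does not by itself remove bias when withdrawal depends on responses that were not observed. Reporting the reasons shows a selective loss but does not repair it.

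A reader might go further and infer that withdrawals would fall in the music arm and favour music, since at visit 1 only that arm can have its music stopped. The documents do not support this. Section 8.3 foresees stopping, by the investigator or the nurse, "who can stop the device at any time", and no section classes stopped music or removed headphones as a major deviation. Other candidate deviations, such as prohibited medication, extra analgesia or a baseline recording under 10 minutes, can occur in either arm.

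**Conclusion.** The conflict between sections 5.3 and 10.2 is real and should be removed. Its importance is low to moderate. It falls mainly on the exploratory endpoints: post-session ratings not yet taken at visit 1, and all of visit 2. It reaches the primary LF/HF value only if a deviation leads staff to stop the visit 1 recording.

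A reader might also infer that section 5.3 removes data, or turns the ITT analysis into a per-protocol one. That is too strong: withdrawal is optional, and data already collected are kept unless consent for their use is withdrawn. The text supports only that later data may not be collected, so that the ITT set could drift towards the per-protocol set. The shifts of 0.05 to 0.29 LF/HF points rest on assumed loss rates and differences and belong to the narrow primary-endpoint case. They are not an estimate of bias in this trial. This conclusion takes all patients in section 10.2 to mean all randomized patients.

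**What to change.** In section 5.3, delete the major-deviation entry from the list of reasons for withdrawal. Add that patients with a major deviation remain in the study, complete the planned visit 1 and visit 2 assessments where they agree, are analysed in their randomized group under ITT, and are excluded only from the per-protocol set. Leave the investigator's health-based discontinuation, intercurrent illness and the subject's own decision unchanged, so that no clinical rule is altered.

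The cost is a line or two of wording and the sponsor's classification of the amendment under section 14.3. No measurement is added to those already planned.
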